Concerning disease-modifying effects, two recent long-term (three years) trials in patients with knee OA did report some evidence that GS affected the progression of OA [6,7]. Progressive joint space narrowing in the narrowest medial compartment of the tibiofemoral joint was used to define progression of knee OA (as recommended by a task force of the OA research society [8]). Whereas joint space narrowing (JSN), had significantly progressed in the placebo groups, it had not in the groups that were taking GS. This implies that daily intake of GS acted against progression of OA. However, these results are controversial, because both trials lacked appropriate and standardised protocols for taking radiographs. Although it is not likely that this influenced the results much [9], it is necessary to reproduce them in a study with well-standardised protocols. These two long-term trials both looked at the effect of GS on knee OA, no trial has been or is being performed yet that looks at its effect on hip OA.

Based on the above, we designed a long-term trial to answer our main question: Does glucosamine sulphate favourably modify progression of osteoarthritis? Because there still is uncertainty about the symptom-modifying properties of GS we will also try to answer three secondary questions: Does GS have the same effects in all stages of OA? What is the long-term cost-effectiveness of addition of GS to usual care? And, does GS prevent the onset or progression of OA in the contralateral hip joint? Additional to these clinical questions, the data will be used to look at changes on cell-level caused by GS to learn more about its possible mechanisms of action. All results derived from this trial will be published using our International Standardised Randomised Controlled Trial Number (ISRCTN).

In this article we will present the detailed protocol of the trial. This trial is ongoing; at the moment all patients are included and have passed the first 9 months of the follow-up period.

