### Sample size

The sample size was calculated primarily to detect clinically relevant differences in radiological progression of the affected joints between the two groups (treatment and placebo) after two years of follow up. To detect a difference of 0.25 mm in radiological progression (SD 0.5) between the intervention and placebo groups (power 80%, alpha 5%, one-tailed testing) after two years of follow-up, 63 patients with hip osteoarthritis are needed per group. These calculations are based on an average change of 0.33 mm in joint space (SD 0.5) during one year of follow-up of patients with hip osteoarthritis [12].

Fewer patients are needed to detect relevant clinical differences: to detect a difference of 25% in pain (Western Ontario McMaster Universities Osteoarthritis index (WOMAC)) with one-tailed testing, a power of 80%, and alpha 5% (Mean 4.83, SD 2.25 [13]) 55 patients per group are needed. To detect the same difference in function (WOMAC) (mean 4.81, SD 2.18 [13]) 51 patients are needed per group.

As we expect a 20% loss to follow-up, we need to include 150 patients. However, to create options for studying effect-modification by type and severity of osteoarthritis, we oversized this trial to 220 patients (110 in each group).

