### Analyses

The researchers will be aware of allocation to treatment A or B at the time of the statistical analyses, but will not know which group received GS and which group received the placebo. All analyses will take place after the trial has finished, no intermediate analyses will be performed.

Success of randomisation and normality of outcome measures will be checked before actual analyses are done. Differences in the primary outcome measures JSN and WOMAC (pain and function) between the intervention and placebo group will be analysed on the basis of the 'intention to treat' principle using linear regression models. Additionally a per-protocol analysis will be done. When it turns out that randomisation was (partially) unsuccessful, we will adjust for differences in prognosis. Using baseline characteristics, we can identify factors that influence outcome of the study. Factors that change the outcome with 10% will be regarded as confounders and will therefore be added to the regression-model.

A cost-effectiveness analysis will be performed from a social and a patient perspective, looking at differences in direct and indirect health care cost between the two groups (GS and placebo). If the trial does not show a difference in disease parameters (WOMAC) and quality of life (EuroQol) between the GS and the placebo group, the analysis will be reduced to a cost minimisation analysis. This form of analysis evaluates the efficacy of treatment based solely on direct and indirect costs. If the study does find a positive difference in disease parameter and/or quality of life a cost-effectiveness ratio can be determined with on the one hand the costs and savings and on the other hand the disease-specific parameters and also quality of life.

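### The economic analysis falls back to cost minimisation when no difference is found, but failing to find a difference does not establish equal effect

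*Protocol article*

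**What the plan says.** Background in the protocol article lists three secondary questions. One of them is "What is the long-term cost-effectiveness of addition of GS to usual care".

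The Analyses section first commits, without condition, to a cost-effectiveness analysis from two perspectives. It then makes the method depend on the result. The trigger is worded "If the trial does not show a difference in disease parameters (WOMAC) and quality of life (EuroQol", and the consequence is that "between the GS and the placebo group, the analysis will be reduced to a cost minimisation analysis". Cost minimisation is described in these words: "This form of analysis evaluates the efficacy of treatment based solely on direct and indirect costs". For the other outcome the text says: "If the study does find a positive difference in disease parameter and/or quality of life a cost-effectiveness ratio can be determined".

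The only comparison of effects described is for the primary outcomes, where differences "will be analysed on the basis of the 'intention to treat' principle using linear regression models". The Sample size section is likewise about finding differences. For WOMAC pain the aim is "to detect a difference of 25% in pain", "with one-tailed testing, a power of 80%, and alpha 5% (Mean 4.83, SD 2.25 [13]) 55 patients per group are needed". The article states no equivalence margin, no confidence-interval criterion for treating the arms as equal, and no sample-size calculation for EuroQol.

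**The concern.** Comparing costs alone is sound when the effects are known to be equal, or close enough for the decision. The rule's condition is weaker: the trial need only have failed to show a difference. With tests of difference as the only tool and no margin, the natural working meaning is that the interval for the difference includes zero. Such an interval can also include differences that matter to a payer or a patient. The rule then treats the effect difference as exactly zero, with no uncertainty.

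At stake is the answer to a named secondary question. GS is added to usual care, so in a costs-only comparison it looks worse unless savings elsewhere offset its price, even if the data are compatible with a worthwhile benefit. In the other direction, GS could look preferable on cost while the data still allow some loss of health.

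**Working it through.** **Inputs**, all from the Sample size section:
- WOMAC pain: mean 4.83, SD 2.25, 55 per group.
- WOMAC function: mean 4.81, SD 2.18, 51 per group.
- Target difference 25%: 0.25 × 4.83 = 1.2075 for pain, 0.25 × 4.81 = 1.2025 for function.
- Recruitment 110 per group and 20% loss: 110 × 0.8 = 88 per group.

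**Step 1: reproduce the plan's figures.** n per group = 2 × [SD × (z for alpha + z for power) / difference]². With two-sided 5% and 80% power, the z values 1.960 and 0.842 sum to 2.802.
- Pain: 2 × (2.25 × 2.802 ÷ 1.2075)² = 54.5, so 55 (stated 55).
- Function: 2 × (2.18 × 2.802 ÷ 1.2025)² = 51.6, so 52 (stated 51).

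The figures match only on a two-sided basis. The one-tailed testing named in the text would give 43 and 41. I therefore use two-sided results below and give one-sided power beside them.

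**Step 2: precision at the end of the trial.** 95% half-width = 1.96 × SD × √(2/n), and √(2/88) = 0.1508.
- Pain: 1.96 × 2.25 × 0.1508 = 0.665 points, or 13.8% of 4.83.
- Function: 1.96 × 2.18 × 0.1508 = 0.644 points, or 13.4% of 4.81.
- With no loss (110 per group): 0.60 points, or 12.3%, for pain and 0.58 points, or 12.0%, for function.

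**Step 3: power for differences below the target (pain).** The standard error is 2.25 × 0.1508 = 0.339. Two-sided power = Φ(difference / SE − 1.96).

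| True difference | Two-sided, n = 88 | Two-sided, n = 110 | One-sided, n = 88 |
|---|---|---|---|
| 10% (0.483) | 30% | 36% | 41% |
| 15% (0.725) | 57% | 67% | 69% |
| 25% (1.2075) | 94% | 98% | 97% |

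For the first cell: 0.483 ÷ 0.339 = 1.42, and Φ(1.42 minus 1.96) = 0.30.

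**Step 4: what it would take to show equivalence.** Two one-sided 5% tests, 80% power, true difference zero: n = 2 × [SD × (z for 95% plus z for 90%) / margin]², where the z values 1.645 and 1.282 sum to 2.927. The plan gives no margin, so these are assumptions.

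| Assumed margin (% of mean) | Pain, n per group | Function, n per group |
|---|---|---|
| 10% | 372 | 352 |
| 15% | 166 | 157 |
| 20% | 93 | 88 |
| 25% | 60 | 57 |

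With 88 to 110 completers per group, equivalence is within reach at margins of about 20% or wider, and not at 10 to 15%.

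**Step 5: EuroQol.** The article gives no SD and no target. If the true standardised difference were 0.2 to 0.3 (an assumption), two-sided power with 88 per group would be 26% to 51%.

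**The case against.** The strongest reply is that the trial is fairly precise on its own terms. The pain half-width of 0.67 points is well below the stated target of 1.21, and power for that target is 94% with 88 per group. An estimate near zero would exclude it. This stands, and it limits the point. But the rule does not ask for that check, and a null result does not guarantee it. The 25% difference is excluded only if the estimate is below 1.2075 − 0.665 = 0.54 points, whereas any estimate below 0.665 counts as no difference. Nor does the reply cover differences of 10 to 15%, or EuroQol.

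A second reply is that the article names no significance test for either branch. That is so; reading the trigger as non-significance is an inference, though no other criterion is offered.

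Three stronger readings are tempting and are not supported:
- A reader might infer that there is no analysis if GS proves worse. The opening commitment to a cost-effectiveness analysis is unconditional, the reduction applies only when no difference is shown, and the sentence on the ratio is permissive. The adverse case is not spelled out; it is not excluded.
- A reader might infer that mentioning a ratio only after a favourable result makes GS look more cost-effective than it is. The article gives nothing from which to calculate such a bias.
- A reader might want the unresolved effect in money. That needs an EQ-5D SD and a willingness-to-pay value, and the article gives neither.

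It is also true that WOMAC and EuroQol are trial outcomes in their own right, so the rule removes them from the economic analysis and not from the trial's results.

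**Conclusion.** The concern holds at moderate weight. The article fixes a rule under which a failure to find a difference is used as if equal effect had been shown, and the effect estimate and its uncertainty then drop out of the economic analysis. With 88 per group, the WOMAC data would leave differences of about 13 to 14% of the mean either side of the estimate unresolved, and a true 10% pain difference would be missed in about 70% of such trials (two-sided). That 70% is for pain alone. The rule also requires EuroQol to show nothing, so it is not the probability that cost minimisation would be triggered.

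The figures assume the Sample size SDs, the expected 20% loss, equal groups and a normal approximation. Adjustment for baseline scores could narrow the intervals. The primary efficacy comparison is unaffected.

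**What to change.** Replace the two conditional sentences in Analyses. Whatever the significance of WOMAC or EuroQol, and whichever arm does better, estimate incremental costs and incremental effects jointly by intention to treat. Keep both effect measures the article plans: EQ-5D-based quality of life and the WOMAC parameters. Report the joint uncertainty, for example with bootstrap intervals and a cost-effectiveness plane. Allow cost minimisation only if equivalence is shown against a margin set before the treatment groups are compared.

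The cost is a little more analysis and agreement on a margin if cost minimisation is to stay available. No extra visits or patients are needed. The Questionnaires section has WOMAC and EQ-5D in all nine questionnaires, and Table 2 shows medical consumption at all nine time points. Table 2 marks WOMAC pain and function only at baseline and 24 months, which is still enough for an end-of-trial difference. The article does not give the timing of the work-related cost items, so that should be confirmed when the analysis is specified.

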### Current status

A total of 40 GP's were found willing to participate in the study. They sent a total of 600 letters to inform possible eligible patients of the study. We received 417 requests for additional information and thus sent an equal amount of information folders. Of these 417 people 250 returned a written informed consent. Eventually 222 people entered the study. Of the 28 people that did not enter the study, most did not meet the inclusion criteria and a few people changed their mind and withdrew their informed consent before randomisation.

We started including patients at the end of September 2003 and the last patient was included on March 15^th ^of 2004. This means the study will run until March 2006. The first results will be available around September 2006.
